Individuals may be included who: report smoking at least 10 cigarettes/day for the previous six months, produce a breath sample with a CO level > 9 ppm, report being motivated to quit, and are able to read and write English. Medical screening at baseline will ensure that participants can safely be prescribed any of the included medications (e.g., no uncontrolled hypertension, history of bipolar illness, recent myocardial infarction, current alcohol dependence with risk of seizure, seizure history, history of bulimia or anorexia nervosa, or current use of a MAO inhibitor). In addition, any individual who reports regular thoughts of suicide or self-harm will be assessed by a clinical psychologist, and those judged to be at risk for suicide will be excluded and offered referrals to appropriate treatment resources.

Figure 1: Treatments for the 1,520 study participants randomized to Project 1: Efficacy For the purposes of this grant application, participants will be considered part of Project 1: Efficacy from the time of their enrollment and completion of pre-quit assessments until their one-year post-quit anniversary date. They will be considered part of the current project (Project 2: Longterm Outcomes) from their one-year post-quit anniversary date until at least three years after the quit attempt anniversary date. Enrollment for Project 1 will take place over the first two years of this five-year TTURC grant. Enrollment in Project 1 will commence about six months after the start of grant funding and will continue for approximately 18 months.

*Enrollment*. Enrollment for Project 2 (Longterm Outcomes) will begin at around 18 months (when the first participant in Project 1 reaches his/her 12 month quit date anniversary) and continues through month 36 (when the last participant in Project 1 reaches his/her 12 month quit date anniversary). The end of Project 1 and the start of Project 2 are designed to be seamless for participants. Based upon cost considerations and power, we will invite only 900 Subjects from Project 1 to participate in Project 2.

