a Vital signs includes carbon monoxide, blood pressure, weight, temperature, pulse, and height at Visit 2. b NCS-R-CIDI, which should last on average 90 minutes, includes a Screener and the following modules: Depression, Irritable Depression, Panic Disorder, Specific Phobia, Social Phobia, Agoraphobia, Generalized Anxiety Disorder, Suicidality, Use of Services, Alcohol Use, Tobacco Use, Chronic Conditions, Neurasthenia, 30-Day Functioning, 30-Day Symptoms, Obsessive-Compulsive Disorder, Worries and Unhappiness. c This will be administered to participants who are married or who have a domestic partner. d Blood will be drawn for the following tests: NMR lipid profile, creatinine, simultaneous fasting blood glucose and insulin, possibly carotenoids, hemoglobin A1C, and high-sensitivity c-reactive protein. e Smoking status includes a review of the abstinence calendar, nature of relapse contexts, use of cessation aids and new quit attempts.

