**Measurement and Data Collection Plan**

For Project 1, baseline questionnaire/interview data as well as physiological assessments will be collected during visits occurring prior to the quit day. This pre-quit data will also provide baseline data for Project 2. In addition to this baseline data, many of these same assessments will be collected at 12, 24, and 36 month (in-person) and 18, 30, and 42 month (telephone) follow-up contacts for Project 2. The timetable for data collected over the three years that comprise Projects 1 and 2 is depicted in Table 4.

*Annual In-Person Clinic Visits (Months 12, 24, and 36).* Participants enrolled in Project 2: Longterm Outcomes will attend an in-person clinic visit at one, two, and three years (12, 24, and 36 months) post-quit attempt. During these visits, participants will repeat many of the baseline assessments (see Table 4) including information to determine continuous and point-prevalence abstinence, the nature of any relapse event (environmental and social context, stressors, alcohol use, and so on), use of any new cessation aids, new quit attempts, and withdrawal and affective status (WSWS, PANAS, etc.). Suicidality will be assessed and appropriate referrals made in the event that suicide risk is determined.

Table 4 also lists other assessments that will take place at each annual in-person visit. Virtually all of the baseline paper-pencil questionnaires will be re-administered as well as the NCS-R-CIDI. In addition, some physiologic measures will be assessed including weight, body mass index, vital signs, waist circumference, and carbon monoxide (provided via a breath sample). Selected physical measures will be collected at some of these visits. For instance, the Carotid IMT, Exercise Stress Test, and NMR LipoProfile tests will be performed at the Baseline and Year 3 Visit. Brachial artery endothelial function will be tested at the Baseline and Year 1. Blood tests will completed at Baseline, Year 1 and Year 3 (but not Year 2) including NMR Lipoprofile, fasting glucose and insulin, hemoglobin A1C, creatinine, high sensitivity C-Reactive Protein, and possibly carotenoids.

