The annual in-person clinic “visits” will occur over two days. The first day will involve assessment administration (questionnaires, simple physiologic measures). The second day will involve more complex physiologic measures including, when indicated, carotid IMT, brachial artery endothelial function, exercise treadmill stress test, and blood tests. Each of the two in-person Follow-up Visits days require about 2 hours (except for Year 2 when only a single day 2 hour visit is required). To ease the assessment burden we will take the following steps: (1) participants may interrupt the assessment session to take breaks, (2) there will be snacks to provide energy and a break from responding, (3) questionnaires may be completed at home if requested, and (4) participants may complete the assessments in multiple visits.

Pedometers will be distributed at the Annual Visits (months 12, 24, 36) along with a weekly recording log and a stamped, padded envelope addressed to the research center. Participants will be instructed to record the pedometer reading each night for a week and then return the pedometer by mail. Participants will receive a reminder phone call the day after they receive the pedometer to encourage daily recordings.

Assessments will be completed using the same procedures as at baseline. For instance, the NCS-R-CIDI will be administered in a computer-assisted format. If the participant is tested outside the research site, study personnel will administer it via laptop computer. Only the medical tests mandate an in-person visit. Finally, an additional visit will occur at 60 months after the quit day, but not within the funding period of this award. As in our previous research, responses on all forms will either be entered via computer (with “catch” criteria) at the time of collection or recorded on scannable forms to minimize the need for manual data entry. When scannable forms are used the researcher will inspect each form as it is completed to reduce scanning errors.

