*Brachial artery reactivity testing (BART):* Endothelial function will be assessed using ultrasound measurement of the brachial artery in response to flow mediated vasodilation (FMD). This dynamic measure of arterial function is impacted immediately by cigarette smoking and is extremely sensitive to rapid changes in risk factors for cardiovascular disease. This will be measured at baseline and at the one-year post-quit attempt visit. Impaired endothelial function is associated with cardiovascular risk factors and prevalent as well as incident cardiovascular disease including among smokers.229-233 This association is dose-dependent, both with increasing pack-years of exposure and varying levels of environmental tobacco smoke. It also seems to be potentially reversible as evidenced by the weaker association seen in former smokers.234 Further studies suggest a synergism between smoking and hypercholesterolemia,232 raising the possibility that smoking potentiates endothelial dysfunction by enhancing LDL oxidation.235,236

Brachial artery endothelial function will be measured noninvasively in the morning in the fasting state by a well-validated technique using high-resolution B-mode ultrasound of the brachial artery.235-239 Subjects who regularly use tobacco-containing products must refrain for 12 hours. After a 10-minute rest in a temperature-controlled room (68-70 F), the diameter of the right brachial artery blood flow are measured at baseline and in response to increased blood flow with a high-resolution (7.5 MHz) linear array vascular ultrasound transducer. Increased forearm blood flow, an endothelium-dependent vasodilator, is induced by inflating a pneumatic blood pressure tourniquet placed around the widest part of the forearm to a systolic blood pressure of 250 mm Hg., the release of which after 4.5 minutes leads to hyperemia. The change in brachial artery diameter in response to hyperemia relative to the baseline diameter defines FMD, which is described as a percentage change from baseline. A single-lead electrocardiogram is monitored throughout the study. Coronary and brachial artery flow-mediated vasodilation are correlated strongly (r=0.79, p<0.001).240 Endothelial function of the brachial artery also predicts future adverse cardiovascular events.235,236 In our laboratory, the coefficient of variation for FMD is 2.9% which compares favorably to that reported in the literature.241-243

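### The 12-hour tobacco rule before the brachial scan covers everyone at baseline but only undefined regular users at Year 1, so change in FMD can mix acute and long-term effects of smoking

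*Protocol*

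**What the plan says.** The paragraph on brachial artery reactivity testing (Protocol, Measurement and Data Collection Plan - Assessments) gives the preparation rule: "Subjects who regularly use tobacco-containing products must refrain for 12 hours". The same paragraph says of FMD: "This dynamic measure of arterial function is impacted immediately by cigarette smoking". It also asks for a morning scan, fasting, after a short rest. None of those conditions mentions tobacco.

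On timing, the Measurement and Data Collection Plan says: "Brachial artery endothelial function will be tested at the Baseline and Year 1".

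On who is scanned, Recruitment and Enrollment admits people who "report smoking at least 10 cigarettes/day for the previous six months". A year later the Project 2 cohort is made up of everyone who reports abstinence, plus a random selection of relapsers. No minimum amount of smoking is set for the relapsers.

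On the visit, simple physiologic measures come first ("The first day will involve assessment administration (questionnaires, simple physiologic measures"). The scan comes later: "The second day will involve more complex physiologic measures including, when indicated, carotid IMT, brachial artery endothelial function". Breath carbon monoxide (CO) is listed among the vital signs in note a to Table 4.

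**The concern.** A 12-hour wait before an FMD scan keeps the passing effect of the last cigarette out of a measurement meant to show the lasting effect of smoking or quitting. That works for a before-and-after comparison only if the same preparation applies both times. Here the rule depends on the participant's usual tobacco use, which is the very thing the study expects to change between the two scans.

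Someone who smoked daily at entry and smokes now and then at Year 1 was told to refrain before the first scan. On a plain reading, that person need not be told to refrain before the second. The same holds for an abstainer who has just lapsed. Any acute effect at Year 1 then goes into that person's change in FMD. Because Year 1 is the only follow-up scan, no later reading can correct it. Unless recent use is recorded at the scan, the affected readings cannot be picked out afterwards.

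**Working it through.** The protocol gives no effect size, standard deviation or power figure for FMD, so there is no stated number to reproduce. The check is mainly textual.

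**1. Whom the rule covers at baseline.** Entry requires at least 10 cigarettes a day for six months. On any reasonable meaning of regular use, every participant is covered.

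**2. Whom it covers at Year 1.** The Human Subjects section defines the abstinent group by self-reported 7-day point prevalence at Week 52. Recruitment and Enrollment takes the rest from relapsers, with no threshold on amount smoked. An occasional smoker is therefore eligible but need not be a regular user. Status for enrolment is taken by telephone, and the in-person visit is scheduled from that call, so a lapse before the scan is possible.

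**3. Whether other text closes the gap.** The description of the annual visits says assessments follow baseline procedures. The baseline procedure is the conditional rule itself, so that statement carries the condition forward without widening it.

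**4. Whether recent smoking is checked at the scan.** No text asks for a CO reading or the time of the last cigarette at the scan, at either time point. The smoking-status review in note e to Table 4 is a general history of abstinence, relapse and quit attempts.

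**5. How many follow-up scans there are.** The text consistently places one at one year. Table 4, as it can be read here, marks the brachial test only at orientation. A mark may have been lost from the table, so I follow the text.

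**6. How the difference enters the analysis.** The Analytic Plan models change through baseline values and change scores, so unequal preparation passes into the estimate.

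**7. Direction and scale, for illustration only.** Let *d* be the acute drop in FMD, in percentage points, after recent smoking. Let *f_A* and *f_S* be the shares of the abstinent and smoking groups scanned at Year 1 after recent use, with baseline scans taken as unaffected.

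- Shift in a group's mean change: −*f* × *d*.
- Shift in the contrast (abstinent minus smoking): (*f_S* − *f_A*) × *d*.

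Neither *f* nor *d* is in the protocol. Assume *f* between 5% and 20% and *d* between 1 and 3 points:

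- Smallest group shift: 0.05 × 1 = 0.05 points.
- Largest group shift: 0.20 × 3 = 0.60 points.
- Only abstainers affected, upper end: (0 − 0.20) × 3 = −0.60, which dilutes the cessation contrast.
- Only smokers affected, upper end: (0.20 − 0) × 3 = +0.60, which exaggerates it.
- Equal shares: the contrast does not move.

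**The case against.** The strongest reply is that this is a loosely worded sentence, and that sites would apply the baseline procedure to everyone. The instruction to repeat baseline procedures can be read that way, but it does not remove the restriction to regular users. A coordinator who follows the text literally need not tell an occasional smoker to refrain.

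Several other points limit the concern and stand:

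- **CO timing.** A reader might infer that the CO reading falls on a different day from the scan. CO is listed with the simple measures ("waist circumference, and carbon monoxide (provided via a breath sample") and among the vital signs ("Vital signs includes carbon monoxide, blood pressure, weight, temperature, pulse, and height at Visit 2"), which suggests the first day. No sentence assigns it to a day, and assessments may be split over several visits. The documents support only that no check at the scan is specified.
- **Baseline compliance.** A reader might infer that baseline scans are known to be free of recent smoking. They are not; compliance is unverified there too. The asymmetry lies in the rule, not in observed behaviour.
- **Direction.** A reader might infer that a cessation benefit must be diluted. That holds for lapsers counted as abstinent, which is a narrow route: smoking before the point-prevalence assessment, if reported or detected, removes a person from that group. Occasional smokers counted as smokers push the contrast the other way.
- **Nicotine products.** A reader might extend the argument to lozenge or gum. The protocol claims an immediate effect for cigarette smoking only, so that extension has no basis in it.
- **Rank.** Hypothesis 1 rests on carotid intima-media thickness. Brachial function is listed under secondary analyses, which the Analytic Plan says will be labelled exploratory if reported. Smoking can also be modelled as a continuous measure, although percent days smoking or a 7-day amount does not give hours since the last cigarette.

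**Conclusion.** The concern holds in limited form. As written, the preparation rule covers every participant at the first brachial scan but can leave out occasional smokers and recent lapsers at the second, for a measure that the protocol describes as immediately responsive to smoking. Change in FMD can then combine acute and long-term effects.

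This is a possible distortion, not a demonstrated one. Its size cannot be obtained from the protocol: the range of 0.05 to 0.60 points for a group mean rests wholly on assumed shares and an assumed acute drop, and the low end would be trivial. Its sign depends on which group the affected people are counted in. It concerns a secondary outcome that Aim 1 names. The carotid hypothesis and both power analyses do not depend on it. The change is worth making because it is cheap and because the affected scans could not be identified later.

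**What to change.** In the brachial artery paragraph, apply the protocol's existing 12-hour tobacco condition to all participants before both scans, whatever their usual use. The term *regularly* then needs no definition.

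At each scan, record the time of last tobacco use. Where convenient, take a breath CO reading at the same time, with the meter already used for the visit. When recent use is found, rebook the scan, or keep it and flag it for a sensitivity analysis that leaves flagged scans out.

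The cost is one revised sentence, one extra recorded item and possibly a short breath test. The downside is a few rebooked or flagged scans; the retention steps already allow rescheduling. This standardises a measurement and changes nobody's treatment.

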**Life After The Quit Attempt - Lifestyle**

*Physical activity & fitness*. Cross-sectionally, both male and female smokers report lower levels of leisure-time physical activity and exercise compared to non-smokers.62-65 Former smokers typically have leisure-time activity levels closer to those of never smokers, than current smokers.63,65,66 Conversely, current smokers tend to have higher levels of occupational activity,63,67 which may be due, in part, to socioeconomic status. Moreover, there is evidence that women who quit smoking adopt a more active lifestyle.68 Additionally, even modest amounts of exercise appear to reduce post-quit weight gain69 and enhance functional capacity.70 These findings suggest that modest amounts of exercise may mitigate potential adverse effects of cessation. Collectively, they suggest that physical activity co-varies with smoking status, and that exercise may be beneficial, at least in women, during quit attempts. Lacking is similar data in men, as well as an understanding of the mechanism by which activity, cessation, and physiological processes lead to vital health outcomes.

Cardiorespiratory fitness is lower in smokers than in non-smokers.71-76 This association is mediated by acute and chronic physiological effects of smoking and a tendency for smokers to be less physically active than non-smokers. However, smoking’s impact on fitness cannot be explained completely by differences in physical activity. Longitudinal data suggest that cardiorespiratory fitness recovers following cessation, and that recovery is greater among men than among women.75,77 Chronotropic incompetence, or an attenuated heart rate response to exercise, also has been associated with smoking among otherwise healthy adults78-80 and may identify smokers with a particularly high mortality rate.80 Blunted heart rate responses have also been identified in young adult smokers undergoing symptom-limited exercise testing/81 Thus, smoking and smoking cessation *appear* to be significantly related to physical activity and cardiovascular fitness, but the potentially complex interplay of smoking/cessation, weight gain, physical activity, and fitness has not been characterized.

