*Physical activity*. This will be quantified using two methods: a physical activity questionnaire and pedometer measurements at baseline prequit, and at the ends of Years 1 & 3. The first is the International Physical Activity Questionnaire that covers all realms of physical activity (occupational, housework, etc.). This instrument has recently been shown to have acceptable reliability (Spearman’s rho = 0.80) and criterion-related validity (rho = 0.30), similar to other physical activity questionnaires.251 Questionnaires, however, tend not to be valid measures of moderate activity such as walking.252 Since walking is the most prevalent leisure-time activity in the U.S., is intrinsic to many daily routines, and is specifically mentioned in current nationwide physical activity recommendations253 it is particularly important to measure this specific activity. Pedometry has proven to be a very reliable and valid measure of steps walked when specific pedometer models are used.254

We propose to measure 7 days of walking annually with a Yamax Digiwalker SW-701. Subjects can be easily and quickly trained in the appropriate use of the pedometer and asked to fill out a simple log to record daily steps over the 7-day period.255 Through the use of both a simple questionnaire and a pedometer, we should be able to capture regular physical activity at targeted timepoints throughout the study.

*Physical fitness*. Each subject will have a symptom-limited treadmill test administered at baseline and at the 3-year follow-up.Peak oxygen consumption will be calculated from the final workload achieved on the test, and oxygen saturation (via pulse oximetry) will be measured at rest and continually during the test. The calculated oxygen consumption provides a measure of fitness, not physical activity, and is therefore a more objective measure than physical activity questionnaires and pedometry monitoring. This provides the opportunity to assess important changes in cardiorespiratory fitness associated with smoking cessation and physical activity.

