While directly measuring oxygen consumption would provide a slightly more accurate assessment, the cost would be much greater. A modified Balke protocol will be used.256 Briefly, each subject will maintain a brisk walking pace and treadmill grade will be increased 2.5% every two minutes until volitional exhaustion. Oxygen saturation and 12-lead electrocardiogram (ECG) will be monitored continuously. ECG, heart rate, and blood pressure will be recorded at the end of each stage, maximum exercise, and every two minutes during recovery. The Borg scale rating of perceived exertion (RPE) ranging from 6 to 20 will be obtained near the end of each stage and maximum exercise. Differences will be compared between subject’s baseline prequit and three year follow-up tests for changes as they relate to smoking status. Changes in fitness based on these treadmill tests will be compared to other changes in the subject’s health status, including body weight, metabolic changes, and health outcomes.

Diet

Dietary factors will be assessed by a combination of a well documented food frequency questionnaire (FFQ), a qualitative screening food frequency questionnaire to track short-term changes, and objective biochemical indicators of diet (NMR Lipoproteins and, possibly, carotenoids).

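### The 12-hour tobacco condition covers only the brachial test, so the baseline-to-Year-3 treadmill comparison of quitters and smokers can include the acute effect of recent smoking

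*Protocol*

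**What the plan says.** The tobacco condition appears once, in the brachial artery procedure (Protocol, Measurement and Data Collection Plan - Assessments): "Subjects who regularly use tobacco-containing products must refrain for 12 hours". On timing, the same paragraph says "This will be measured at baseline and at the one-year post-quit attempt visit", and the Measurement and Data Collection Plan agrees: "Brachial artery endothelial function will be tested at the Baseline and Year 1". Table 4 marks the brachial test at orientation only. No version places it at Year 3.

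The treadmill schedule differs: "Each subject will have a symptom-limited treadmill test administered at baseline and at the 3-year follow-up". During the test, "ECG, heart rate, and blood pressure will be recorded at the end of each stage", and also at maximum exercise and in recovery. Neither this procedure nor the stress-test screening under Protection Against Risk sets a condition on recent smoking. The 12-hour fast before the blood draw does not mention tobacco. Baseline results are then to be compared with the "three year follow-up tests for changes as they relate to smoking status".

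The background section (Life After The Quit Attempt - Lifestyle) says of the lower fitness of smokers: "This association is mediated by acute and chronic physiological effects of smoking".

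**The concern.** The Protocol recognises an acute and a chronic part in smoking's effect on fitness. It controls the acute part for one vascular test and leaves it open for the fitness test. At baseline everyone smokes. At Year 3 only continuing smokers do, and nothing stops them from smoking shortly before the test. A better treadmill result in quitters could then reflect partly three years without cigarettes and partly a comparison group that had smoked that morning.

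The comparison is meant to show fitness change associated with cessation and to relate it to weight, metabolic change and health. If time since the last cigarette is not recorded, no later analysis can separate the two parts. That makes this a matter for the visit instructions, not for a statistical analysis plan.

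**Working it through.** The Protocol states no sample size, power or effect size for treadmill outcomes, so there is no figure to reproduce. The check is algebra on the difference in change.

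**Definitions.** LQ and LS are the long-term changes in quitters and continuing smokers. a0Q and a0S are the mean acute effects at the baseline test in those who later quit and those who go on smoking. a3 is the mean acute effect in continuing smokers at Year 3. Quitters have no acute effect at Year 3.

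- Quitter change = LQ − a0Q
- Smoker change = LS + a3 − a0S
- Difference = (LQ − LS) − a3 + (a0S − a0Q)

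If the baseline acute effect is equal in the two groups, the last term is zero and the difference is (LQ − LS) − a3. The baseline effect cancels between groups; the Year 3 effect does not. For fitness, a3 is negative on the Protocol's own account, so the apparent advantage of quitting grows.

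**Numerical check**, in arbitrary units: LQ = 1, LS = 0, acute effect −1 where present. The true difference is 1.

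| Acute effect at baseline (both groups) | Acute effect at Year 3 (smokers) | Quitter change | Smoker change | Difference |
|---|---|---|---|---|
| none | none | 1 | 0 | 1 |
| none | −1 | 1 | −1 | 2 |
| −1 | none | 2 | 1 | 1 |
| −1 | −1 | 2 | 0 | 2 |

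The group difference is wrong in exactly the rows where smokers carry an acute effect at Year 3. The baseline state changes the within-quitter change (1 or 2) but not the group difference, as long as it is equal in both groups.

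**Illustration of consequence.** The acute effects below are assumptions. The group sizes, 300 continuously abstinent and 450 smoking, come from the Power section and may be larger than the number with two treadmill tests.

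- SE of the difference, in SDs of the change score = √(1/300 + 1/450) = √0.005556 = 0.0745.
- With no long-term effect and an acute effect of size a, the chance of a significant result at two-sided 0.05 is Φ(a/SE − 1.96) + Φ(−a/SE − 1.96).

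| Assumed a (SD) | a/SE | Chance of a significant difference |
|---|---|---|
| 0.05 | 0.67 | 10% |
| 0.10 | 1.34 | 27% |
| 0.15 | 2.01 | 52% |
| 0.20 | 2.68 | 77% |

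The value a is an average over all continuing smokers, so it is smaller if many of them had not smoked recently. A larger sample does not reduce it; it only makes the false difference easier to detect.

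**The case against.** **Follow-up repeats baseline procedures.** The Measurement and Data Collection Plan says so. If baseline treadmill testing shared the tobacco-free brachial session, repeating that condition at Year 3 would remove a3. This is a fair reading, but the document does not secure it. The sentence sets no tobacco rule for the treadmill, and the grouping of complex tests on a second day describes the annual visits. Baseline consists of orientation visits in Project 1, whose document is not shown. For the same reason, a reader might infer that every possible baseline layout biases the result towards cessation. That does not follow, because equal abstinence at both tests is also possible.

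**Preparation may be set elsewhere.** The stress-test screening refers to physician-reviewed protocols, and these might cover tobacco. They are cited for contraindications, and nothing in the Protocol says that they do.

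**The acute effect may be part of the target.** Continuing smokers normally exercise while smoking, so fitness in their usual state is a legitimate quantity, and the wording of the comparison does not exclude it. This stands as far as it goes: the Protocol must say which effect it wants. The project's subject is long-term outcomes, and the brachial procedure already excludes recent smoking, so the longer-term effect is the more natural reading.

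**CO is already collected.** Breath CO is among the vital signs, but simple measures fall on the first day of an annual visit and the treadmill on the second. A reading from the treadmill session is not assured.

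**Resting heart rate and blood pressure.** A reader might extend the point to these. The documents do not support that: resting measures appear to belong to the first day, outside the session at issue.

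**Conclusion.** The point holds for treadmill outcomes, including heart rate and blood pressure recorded during the exercise test. As written, the quitter-versus-smoker difference in treadmill change can include the acute effect of recent smoking in continuing smokers at Year 3. The shift equals the mean of that effect. Its size is not given, depends on how recently those smokers smoked, and could be small. The SD figures above show sensitivity and are not estimates.

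The result assumes an equal baseline acute effect in the two groups; otherwise the term (a0S − a0Q) is added. The direction is supported for fitness only. For exercise heart rate and blood pressure the Protocol gives no direction, so the supported claim is confounding by recent smoking.

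Two stronger readings should be resisted. One is that the bias favours a hypothesis of the study: treadmill fitness is listed under secondary analyses, no principal hypothesis predicts treadmill change, and Hypothesis 1 rests on carotid IMT. The other is that all of the roughly 450 smokers are affected: that would require each to have smoked shortly before testing, which the document does not say. The defect should be corrected because it cannot be repaired after data collection, but it does not touch the principal hypotheses.

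**What to change.** 1. Apply the tobacco condition already used for the brachial test equally to the baseline and Year 3 treadmill sessions. The Year 3 session matters most for the group contrast; the baseline session matters for the change within quitters and for any baseline imbalance.
2. At each treadmill session, log time since last cigarette and breath CO.
3. State that the treadmill comparison by smoking status targets the longer-term effect.
4. Use time since last cigarette descriptively, or in a sensitivity analysis among continuing smokers. Do not adjust the quit-versus-smoke contrast for Year 3 CO: it marks current smoking, so adjustment would remove part of the contrast itself. Do not restrict to participants in the same tobacco state at both tests either, because 12 hours without tobacco at baseline is not the same state as three years' abstinence.

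The cost is one line in the visit instructions and two logged items, with no new type of procedure. The downside is some inconvenience and rescheduling, and possible withdrawal symptoms in continuing smokers during a maximal test. The logged items would let that be described.
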